### Trial design

The prospective, single-centre RCT will enrol 54 participants that will be randomised in a 1:1 ratio to the experimental group (vitrectomy combined with lens capsule flap transplantation) or control group (vitrectomy combined with ILM tamponade). The patient’s ophthalmic and systemic medical history and first examination results at admission will be recorded during the screening visit for the trial. Vitrectomy combined with lens capsule flap transplantation or ILM tamponade will be performed by one experienced surgeon. The protocol (date: 24 June 2022, version: 1.1) was developed and updated in accordance with the Consolidated Standards of Reporting Trials guidelines. This protocol was written in accordance with the Standard Protocol Items: Recommendations for Interventional Trials guidelines^26^ and was approved by the Institutional Review Board of Shanghai General Hospital (online supplemental file 1), approved ID: 2022SQ284.1). The trial has been registered with the Chinese Clinical Trial Registry (ChiCTR; http://www.chictr.org.cn/, No. ChiCTR2200057836). Any protocol modifications will be communicated to the participants and trial registry. Trial results will be disseminated on trial registration (ChiCTR) or through a publication. Participants have the right to withdraw their consent and discontinue participation at any time. A flow chart of the trial design is shown in figure 1.

10.1136/bmjopen-2022-064299.supp1Supplementary data

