### Interventions

All participants who meet the inclusion criteria of this study and do not meet any of the exclusion criteria can be included in this study. Before the surgery, the patients should receive complete preoperative ophthalmic examination, including best corrected visual acuity (BCVA), slit lamp inspection, axial length, presence of staphyloma, myopia dioptres, intraocular pressure (IOP), ocular B-ultrasound, OCT, multifocal electrophysiology (mfERG), MP-1 microperimeter, fluorescence fundus angiography and indocyanine green angiography. After passing the screening, the participants who provided written informed consent will be randomly assigned to two parallel trial groups in a 1:1 ratio according to the central randomisation system. The patients will undergo vitrectomy combined with lens capsule flap transplantation or ILM tamponade and regular postsurgery follow-up. Participants will be blinded to the specific surgical methods. The timeline of data collection is shown in table 1.

**Table 1 T1:** Outcome measurements and data collection at each follow-up timepoint

Phase		Screen	Preoperative examination	Postoperative follow-up					
Follow-up		1	2	3	4	5	6	7	14
Time points		Within 1 week before operation	One day before operation	1 day after operation	3 days after operation	7 days after operation	1 month after operation	3 months after operation	6 months after operation
Informed consent		●							
Inclusion and exclusion criteria		●							
Withdrawal criteria			●	●	●	●	●	●	●
Medical history collection		●							
Ophthalmic examination	BCVA	●	●	●	●	●	●	●	●
	Slit lamp inspection	●	●	●	●	●	●	●	●
	Axial length	●						●	●
	Presence of staphyloma	●						●	●
	Myopia dioptres	●						●	●
	IOP	●	●	●	●	●	●	●	●
	Ocular B-ultrasound	●	●	●	●	●	●	●	●
	OCT	●	●	●	●	●	●	●	●
	mfERG	●						●	●
	MP-1 microperimeter	●						●	●
	FFA and ICGA	●							●
Systemic	Vital signs	●	●	●	●	●	●	●	●
examination	Physical examination	●							●
Laboratory examination	routine blood test	●	●				●		●
	Blood biochemistry	●					●		●
	Coagulation function	●							●
	Urinalysis	●							●
	Immune and infection measurements	●				●	●		●
	ECG	●							●
	Chest CT	●							●
Adverse events recorded		●	●	●	●	●	●	●	●

BCVA, best corrected visual acuity; IOP, intraocular pressure; OCT, optical coherence tomography; mfERG, multifocal electrophysiology; FFA, fluorescence fundus angiography; ICGA, indocyanine green angiography.

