### Secondary outcomes

The following indicators will be used to comprehensively assess anatomical outcome: (1) type I closure rate of MH 3 months after operation; (2) type II closure rate of MH 6 months after operation; and (3) type II closure rate of MH 3 months after operation.

Functional outcomes will be assessed as follows: (1) changes in BCVA 3 and 6 months after operation compared with baseline; (2) changes in P1 wave response density in the macular region 3 and 6 months after operation compared with baseline; and (3) changes in macular retinal sensitivity 3 and 6 months after operation compared with baseline.

Furthermore, the number of adverse events and reactions, abnormality of ophthalmic examination, abnormal systemic symptoms and laboratory results will be recorded at each follow-up visit.

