### Statistical analysis

SPSS (V.22.0; SPSS, Inc) and GraphPad Prism (V.8, GraphPad software Inc, San Diego, California, USA) will be used for data processing and analyses. Categorical variables will be expressed as numbers and frequencies, and between-group differences will be evaluated with Fisher’s exact test. Continuous variables will be expressed as the mean±SD. The Kolmogorov-Smirnov test will be used to determine whether continuous variables are normally distributed. The Student’s t-test will be used for normally distributed data, and the Wilcoxon signed-rank test will be used for non-normally distributed data. All statistical tests will be two-sided with p<0.05 considered statistically significant.

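### The only test named for non-normal continuous data is a paired one (Wilcoxon signed-rank), so non-normal functional outcomes have no usable comparison between the two independent arms

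*Protocol article*

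**What the plan says.** The Statistical analysis section sets a two-branch rule for continuous variables, decided by a Kolmogorov-Smirnov test. On one branch, "The Student’s t-test will be used for normally distributed data"; on the other, "the Wilcoxon signed-rank test will be used for non-normally distributed data". It does not say whether the t-test is paired or independent-samples, or which comparison either test serves. The only words in that section about comparing groups belong to categorical variables: "between-group differences will be evaluated with Fisher’s exact test".

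The design is not paired. Under Interventions, patients are "randomly assigned to two parallel trial groups in a 1:1 ratio according to the central randomisation system", and Trial design describes the same 1:1 allocation. Randomisation is stratified by macular hole size (above 400 µm or not), which creates strata and not matched pairs.

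The continuous efficacy outcomes under Secondary outcomes are "changes in BCVA 3 and 6 months after operation compared with baseline", "changes in P1 wave response density in the macular region 3 and 6 months after operation compared with baseline", and the same change in macular retinal sensitivity. The Overview states a comparative hypothesis that covers functional recovery as well as reattachment.

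**The concern.** The signed-rank test works on differences within matched pairs, or on one sample of differences. The rank-based counterpart of an independent-samples t-test is the rank-sum (Mann-Whitney) test, which the article does not name. As written, the non-normal branch leads to a test that either cannot be applied between these arms or, applied within each arm, does not compare them.

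At stake is the functional part of the hypothesis: three outcomes at two time points each. If the prespecified test turns out to be unusable, the analyst must choose another after the data are in, which is what prespecification is meant to prevent. If it is run within each arm instead, there is a temptation to read significance in one arm and not in the other as a treatment effect.

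**Working it through.** **The plan's own figure.** The sample size (96% v 65%, two-sided 5%, power 0.80) is 21 per group. The arcsine formula gives n = 2(1.96 + 0.84)²/h², with h = 2·asin√0.96 − 2·asin√0.65 ≈ 0.863, so n ≈ 21.06. The unpooled normal approximation gives 21.7. Then 21/0.80 = 26.25, rounded up to 27 per group and 54 in total. The plan's figure is reproduced to within a patient. It rests on the binary primary outcome and supplies only the arm sizes used below.

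**Step 1: can the test be run between arms?** It needs equal numbers. With 21 v 20 values the software call returns an error. Assume each of 27 patients per arm completes independently with probability p. Then P(equal arms) = Σₖ [C(27,k) pᵏ (1−p)²⁷⁻ᵏ]².
- p = 0.80 (the plan's 20% attrition): 0.136.
- p = 0.95: 0.26.

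In most trials the test could not be computed between arms.

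**Step 2: if the arms happen to be equal, is the p-value determined?** It is not, because it changes with the order in which unrelated patients are lined up. Three simulated data sets (none from the trial):

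| Patients per arm | Rank-sum p | Signed-rank p over random row orders |
|---|---|---|
| 24 | 0.031 | 0.0007 to 0.12 (3,000 orders) |
| 24, similar data | about 0.031 | 0.0002 to 0.17; median 0.031, middle half 0.018 to 0.046 |
| 21 | 0.84 | 0.27 to 1.00 (5,000 orders) |

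The ranges are extremes, and the middle half is much narrower. Even so, one data set can fall on either side of 0.05.

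**Step 3: error rates under arbitrary pairing.** Simulated lognormal outcomes, log-SD 0.8, with an additive shift of 0.6 as the alternative (6,000 trials per setting):

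| Patients per arm | Type I error, signed-rank | Type I error, rank-sum | Power, signed-rank | Power, rank-sum |
|---|---|---|---|---|
| 21 | 0.050 | 0.048 | 0.49 | 0.68 |
| 27 | 0.048 | 0.048 | 0.60 | 0.79 |

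False positives are not inflated. The power loss is 18 to 19 points under this model. It is model-dependent: with a shift on the log scale it is only about 5 points.

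**Step 4: if the test is used within each arm.** It then tests change from baseline separately in each arm and yields no between-arm p-value. If both arms improve equally and each within-arm test has power w, exactly one is significant with probability 2w(1−w), which peaks at 0.50 when w = 0.50. Simulation agrees: 49.8% with a true change of 0.5 SD and 21 per arm, and 48.6% with a skewed distribution. Both effect sizes are assumptions.

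**The case against.** The strongest defence is that the article never says the signed-rank test is used between arms. The reference to group differences is attached to categorical data only, the type of t-test is open, and the functional outcomes are changes from baseline, for which a signed-rank test within patients is legitimate. This stands as far as it goes: a reader might infer that the plan definitely tests one arm against the other with a paired test, and the text does not establish that. It does not rescue the sentence. The article does not confine the test to within-patient change, and on that reading non-normal outcomes have no between-group test although the hypothesis is comparative. Nor is this merely detail left to a fuller document, since the article names a test for the purpose and names an unsuitable one.

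Second, it is tempting to call the result an invalid p-value in the sense of too many false positives. The simulations contradict this: type I error is about 0.05 under arbitrary pairing. With unequal arms the analyst would meet an error message and not a silently wrong answer, which limits the harm.

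Third, a reader might infer that every functional outcome will be analysed this way. That depends on the normality test rejecting. In simulations with 21 to 27 per arm, moderate skew (lognormal, log-SD 0.5) was rejected about 2% of the time by the uncorrected Kolmogorov-Smirnov test and 35 to 45% with the Lilliefors correction. Strong skew (log-SD 0.8) gave 11 to 17% and 67 to 77%. The article gives no distributions for these outcomes, so the t-test branch may often be the one used.

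Fourth, the discordance of about 50% describes a procedure that the plan does not state. It shows why within-arm tests cannot stand in for a comparison, and it does not measure the harm of the sentence as written.

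**Conclusion.** The point holds with limited reach. The article prespecifies a paired test as its only method for non-normal continuous data in a trial of two independent arms, and neither reading of the sentence yields a usable between-group comparison. Between arms, the test could not be computed in roughly 86% of trials (1 − 0.136), assuming independent completion at 80%. When it can be computed, the result is arbitrary in row order and costs some 5 to 19 points of power under the assumed models, without inflating type I error.

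The effect is confined to continuous secondary outcomes (changes in BCVA, P1 response density and macular sensitivity) that fail the normality test. The documents give no ground for extending it to the primary outcome, which is binary and tested with Fisher's exact test, or to the sample size built on it. The sentence may well be a slip of one term for another. It should be fixed, but it does not threaten the trial's main result.

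**What to change.** In the Statistical analysis section:
- Name the Wilcoxon rank-sum (Mann-Whitney U) test in place of the signed-rank test for between-group comparisons of non-normal continuous data, including changes from baseline.
- State that Student's t-test is the independent-samples version.
- If the signed-rank test is kept, limit it explicitly to descriptive change within a group.

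A Hodges-Lehmann difference with a 95% confidence interval would be a useful addition, but it is optional.

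The cost is a sentence or so. SPSS and GraphPad Prism, the packages the plan names, both offer the rank-sum test. Design, sample size and data collection do not change. The article describes the trial as still in preparation, so the correction can be made before any outcome data exist.

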## Ethics and dissemination

This RCT has been designed in accordance with the principles of the Declaration of Helsinki. The trial protocol has been approved by the Shanghai General Hospital Institutional Review Board (Approval ID: 2022SQ284.1). It is registered on the primary registry of the WHO registry network (Chinese Clinical Trial Registry). Signed consent will be obtained from each patient after they have been informed of the study procedures, possible risks and their right to withdraw from the trial. The results of the trial without personal data will be directly communicated to participants and to the public through peer-reviewed publications and conference presentations. Standard and on-site screening are being conducted by an experienced retinal surgeon. Anaesthesiologists will monitor the whole surgical process.

### Trial status

This study is currently in the preparatory stage. The first participant will be enrolled in April 2023. The projected completion date is March 2025.
